#### Statistical exemplification

The following analysis estimates the treatment efficacy of the two implementation conditions using random effects multilevel models [89]. To consider the variance components at each level (assessment times nested in patients and therapists), we will conduct 3-level models where the repeated assessments of the primary outcome at level 1 will be nested within patients at level 2 and therapists at level 3 (for a comparable model see e.g. [92]). Using a step-by-step approach [91], the growth models potentially will end up in a multi-predictor model to investigate the main outcome-predictors at each level simultaneously. An example of such a model is: At Level 1 (assessment level),

*PSWQ*_*ijk*_ = *π*_0*jk*_ + *π*_1*jk*_(time) + *e*_*ijk*_

where *PSWQ*_*ijk*_ is the estimated value of the Penn State Worry Questionnaire (PSWQ) within a time-specific assessment of each patient_j_ and therapist_k_; *π*_*0jk*_ represents the intake-centered intercept of the repeated PSWQ-measures within each patient; *π*_*1jk*_ (time) represents the decrease of symptoms from pretreatment up to post-treatment, and *e*_*ij*_ represents the corresponding error term.

At Level 2 (patient level),

for intercept: *π*_0*jk*_ = *ß*_00*k*_ + *ß*_01*k*_(number of comorbidities) + *r*_0*jk*_.

for time: *π*_1*jk*_ = *ß*_10*k*_ + *ß*_11*k*_(implementation condition) + *r*_1*jk*_*.*

where *π*_*0jk*_ is the estimate of the true population overall patients’ intake PSWQ and *π*_*1jk*_ is the estimation of the overall symptom reduction across the repeated assessments. Further, *ß*_*00k*_ and *ß*_*10k*_ are the estimated overall grand means of PSWQ intercept and time, and *ß*_*01k*_(number of comorbidities) and *ß*_*11k*_(implementation condition) represent the specific patients’ level predictors on intercept *π*_*0jk*_ and growth *π*_*1jk*_ respectively*.* Finally*, r*_*0j*k_ and *r*_*1jk*_ are the corresponding error terms at the patients’ level.

At Level 3 (therapist level):

*ß*_00*k*_ = *γ*_000_ + *u*_00*k*_

*ß*_01*k*_ = *γ*_010_

*ß*_10*k*_ = *γ*_100_

*ß*_11*k*_ = *γ*_110_ + *γ*_111_(therapists^’^ implementation preference) + *u*_11*k*_

where *ß*_*00k*_ is the estimate of the true population therapists’ overall intake PSWQ and *ß*_*10k*_ is the corresponding overall true population symptom reduction *among therapists*; *ß*_*01k*_ and *ß*_*11k*_ are the overall therapists’ true population estimations of the level 2 predictors. Furthermore, *γ*_*000*_ and *γ*_*100*_ are the estimated overall grand means of PSWQ intercept and time at therapists’ level, *γ*_*111*_ (therapists’ implementation preference) is the hypothesized therapists’ preference on the implementation condition *ß*_*11k*_. Finally, *u*_*00k*_ and *u*_*11k*_ are the corresponding error terms at the therapist level (see also [6, 93] for a conceptual frame).

The various multi-predictor models will be compared using Akaike information criterion (AIC) and the Bayesian information criterion (BIC; see [88]) and deviance test of variance components respectively [89].

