### Aims of the implementation trial

Rather than contrasting increasing numbers of new overall treatment-packages, an additional approach may be to increase the understanding of fine-grained implementation strategies within already effective psychotherapies. Such research questions require the development of novel randomized clinical implementation designs that simultaneously investigate potential implementation effects along with therapist as well as patient effects [5].

This trial investigates two different implementation strategies of customizing a bona fide psychotherapy based on a well-introduced CBT-protocol for GAD [39]. The patients will be randomly assigned to two implementation conditions: (1) a systematic focus on subtle changes lasting from 7 to 20 min at the check-in phase of every psychotherapy session [61, 65]; and (2) a state-of-the-art (SOTA) check-in phase lasting several minutes mainly focused on the session goals. Potential therapists’ implementation effects will be examined based on an ABAB therapist allocation (see design). The main research questions are as follows:Practicability: Is the newly developed randomized clinical implementation trial design and particularly the therapists’ ABAB allocation practicable (ABAB crossed-therapist design), and what are the specific challenges when conducting such a structured design at the patient as well as therapist level?Post-session outcomes: Are there differences in process evaluations measured by post-session reports for the two implementation conditions? Furthermore, are early post-session outcomes predictors of symptom change and mediators of ultimate therapy outcome (e.g. [66])?Treatment outcomes: What are the differences in the treatment efficacy of the two randomized implementation conditions, (1) in dropout rates, (2) in self-reported primary and secondary outcomes [64]?Therapist effects: Are the implementation effects robust across therapists? Is there an interaction effect between potential therapists’ preferences for a particular implementation condition and outcome?

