## Methods/design

### Design

It is a common data structure in human interventions that patients are nested within therapists. The proposed randomized controlled design systematize both levels, i. e. patient as well as therapist level (Fig. 1 for the nested design):At patient level: Eighty patients will be allocated within a traditional 2 × 4 randomized controlled design with one between-subject factor (systematic focus on subtle changes vs. SOTA check-in phase) and one within-subject factor (assessment times: pre-, intermediates-, post-treatment and follow-ups).At therapist level: Twenty therapists will each conduct four therapies using an ABAB-design randomly starting with a SOTA check-in phase or a systematic focus on subtle changes (80 patients). Overall, this ABAB crossed-therapist design allows us to integrate across what might be considered single case studies of 20 therapists [67]. An advantage of this design is, that within-subject effects can be estimated. However, multiple observations may also lead to learning effects, and potential carry over effects may be detected from the therapist’s first to the fourth therapy. Most importantly, however, such therapist effects are not considered as effects that have to be eliminated. Rather, the longitudinal, multilevel design allows us to estimate therapist effects in parallel to the implementation effects [5].

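### The written-out three-level model gives every therapist the same overall slope and omits the preference main effect, so it cannot estimate overall therapist differences in change, and the meaning of its interaction term depends on an unstated coding

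*Protocol article*

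**What the plan says.** The section Statistical exemplification gives one explicit model for the PSWQ, with assessments nested in patients and patients in therapists. At the patient level the slope is π1jk = β10k + β11k(condition) + r1jk. The therapist-level equations that matter here are:

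- Intercept: "ß*_00*k*_ = *γ*_000_ + *u*_00*k". The patient intercept π0jk "represents the intake-centered intercept of the repeated PSWQ-measures within each patient".
- Overall slope: "ß*_10*k*_ = *γ*_100", with no residual and no predictor.
- Condition effect on the slope: "ß*_11*k*_ = *γ*_110_ + *γ*_111_(therapists^’^ implementation preference) + *u*_11*k".

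The text then says that u00k and u11k "are the corresponding error terms at the therapist level" and names no others. The same paragraph nevertheless speaks of β10k as a reduction in symptoms across therapists. The model is introduced as an example reached step by step, and candidate models are to be compared by AIC, BIC and deviance tests. The coding of condition is not given.

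On purpose, the Design section says that the longitudinal multilevel design "allows us to estimate therapist effects in parallel to the implementation effects", and the Background says that crossing lets overall therapist effectiveness be compared across conditions. Research question 4, in the Aims, asks whether implementation effects hold across therapists, and whether there is an interaction involving therapists' "preferences for a particular implementation condition and outcome". On size: "Twenty therapists will each conduct four therapies using an ABAB-design", which gives 80 patients.

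**The concern.** The intercept is the intake level, so u00k describes which patients a therapist received, not what the therapist achieved. A therapist who is better in both conditions would show up in a random term on the overall slope, and that term is absent. A preference that goes with better or worse results in both arms would show up as a preference effect on the overall slope, and that is absent too. The Background itself allows that preference may bear on a therapist's effectiveness across conditions.

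An interaction fitted without its main effect changes meaning with the coding of the factor. What is at stake is the answer to research question 4, and the estimate of overall therapist effectiveness for which the crossed design was chosen.

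**Working it through.** **1. Substitution.** With C for condition and P for preference, the printed levels give

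slope = γ100 + C·(γ110 + γ111·P + u11k) + r1jk.

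Therapist and preference reach the slope only when multiplied by C.

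**2. Coding 0/1.**
- Arm coded 0: slope = γ100 + r1jk, so there is no therapist variation and no preference effect.
- Arm coded 1: slope = γ100 + γ110 + γ111·P + u11k + r1jk, so γ111 is the preference effect within that arm.

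If the truth is a preference effect b in both arms with no interaction, γ111 estimates b. Recoding the other arm as 1 gives b again with the same sign, whereas a true interaction would change sign.

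**3. Coding ±0.5.** Therapist deviations are +0.5·u11k and −0.5·u11k, a correlation of −1. The preference effects are forced to +0.5·γ111 and −0.5·γ111. Fitting a true (b, b) in a balanced design minimises (b − 0.5γ111)² + (b + 0.5γ111)², which gives γ111 = 0. No false interaction arises.

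**4. Simulated size of the false interaction.** From the article: 20 therapists, 4 patients each in alternating sequence, α = 0.05 (taken as two-sided). Assumed, because the article gives no figures: patient slope residual variance 1, standardised preference, preference main effects of 0 to 0.5 SD, therapist share of slope variance 5%, no true interaction and no true therapist-by-condition variance. Fitted by REML with an 18-df t test; 1,000 runs for the printed model and 400 for the corrected one. The corrected model adds γ101 and u10k.

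| Main effect | Printed, 0/1: mean γ111 | Printed, 0/1: rejected | Printed, ±0.5: mean γ111 | Printed, ±0.5: rejected | Corrected, 0/1: rejected | Corrected, ±0.5: rejected |
|---|---|---|---|---|---|---|
| 0 | 0.007 | 2.5% | 0.010 | 3.7% | 4.3% | 3.5% |
| 0.2 | 0.196 | 16.3% | 0.001 | 3.2% | 5.2% | 2.8% |
| 0.3 | 0.293 | 31.6% | 0.004 | 2.7% | 4.3% | 4.5% |
| 0.5 | 0.501 | 71.3% | 0.009 | 2.2% | 5.0% | 3.3% |

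Monte Carlo standard errors: √(0.316 × 0.684/1000) ≈ 1.5 percentage points, and √(0.04 × 0.96/400) ≈ 1 point.

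A full three-level fit to one simulated data set of 200 therapists (main effect 0.3, interaction 0) agrees. The printed model with 0/1 coding gives γ111 = 0.30 (p = 2 × 10⁻⁶), the corrected model 0.085 (p = 0.33), and the printed model with ±0.5 coding 0.085 (p = 0.35).

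**5. Effect on the u11k variance.** Mean estimates when the true value is 0 and there is no preference effect:

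| Therapist share | Printed, 0/1 | Corrected, 0/1 | Printed, ±0.5 | Corrected, ±0.5 |
|---|---|---|---|---|
| 0% | 0.067 | 0.074 | 0.146 | 0.201 |
| 5% | 0.098 | 0.084 | 0.133 | 0.157 |
| 10% | 0.141 | 0.101 | 0.102 | 0.161 |
| 20% | 0.207 | 0.098 | 0.056 | 0.183 |

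A variance estimate cannot be negative, so the mean is above 0 even with no therapist effect; the first row is the baseline. Against it, general therapist variance inflates u11k under 0/1 coding and pushes it toward zero under ±0.5 coding.

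The corrected model recovers the general therapist variance. The true values are 0.10/0.90 = 0.11 and 0.20/0.80 = 0.25; the mean estimates are 0.11 to 0.13 and 0.25 to 0.26.

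**6. Condition contrast.** A separate simulation (1,500 runs, total slope variance 1) compared the printed structure under 0/1 coding with the fuller one. The ratio of standard errors is 0.2295/0.2217 = 1.035 at a 10% therapist share and 0.2313/0.2088 = 1.108 at 20%. Power for an assumed 0.5 SD effect is 0.58, against 0.62 and 0.66. In the simulation behind step 5, the printed model under 0/1 coding rejects a true null for condition in 1.4% of trials at a 20% share, so that test is conservative.

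**The case against.** The strongest reply is that this is a worked illustration in a condensed article. The section says the models are built step by step and compared by information criteria and deviance tests, so the missing terms could be added. The first half of research question 4 asks whether the condition effect varies over therapists, and u11k is the right parameter for that. The false interaction needs both 0/1-type coding and a real preference main effect, and the article states neither.

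Much of this stands and lowers the severity. It does not remove the point. This is the only model written out, and its equation for β10k conflicts with the article's own description of that term. Nor can model comparison be relied on to repair it. In simulations from the printed model with 0/1 coding and no true interaction (300 runs per setting), a deviance test added u10k in 9%, 15% and 43% of trials at therapist shares of 5%, 10% and 20%. With a true preference main effect of 0.3 SD, BIC added the preference term in 36% to 41% and AIC in 60% to 65%.

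Three stronger readings are tempting, and the documents do not support them:

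- A reader might infer that the model has no therapist effect on change and cannot estimate therapist effects at all. It does contain one, u11k on condition by time; only the general slope effect is missing.
- A reader might infer that research question 4 must get a wrong answer. That depends on the coding and on an actual preference main effect; omitting u10k alone left the γ111 test at 2% to 5%.
- A reader might infer that general therapist variance enters u11k under any coding. Under ±0.5 coding it does the reverse.

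**Conclusion.** The point holds for the printed model. It cannot estimate overall therapist differences in symptom change, which the Background and Design sections present as a purpose of crossing therapists. Until the coding is stated, γ111 and u11k have no settled meaning. Under 0/1 coding, a preference main effect of 0.2 to 0.5 SD would be reported as a significant interaction in about 16% to 71% of trials. Under ±0.5 coding the interaction test is sound, but a therapist who does better in one arm is made to do worse in the other by the same amount.

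These sizes rest on assumed preference effects and therapist shares, not on figures in the article. The main condition contrast is only modestly affected, and in the conservative direction. This should be fixed; it bears mainly on research question 4 and does not threaten the comparison of conditions.

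**What to change.** Write the therapist-level slope equations as

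- β10k = γ100 + γ101(preference) + u10k
- β11k = γ110 + γ111(preference) + u11k

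State the coding of condition, preferably centred at −0.5/+0.5. Keep γ101 and u10k in the model whenever γ111 and u11k are interpreted for research question 4, whatever the information criteria favour. With γ101 present, γ111 is a true interaction under either coding. Estimating the covariance of u10k and u11k is optional.

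The cost is a change of analysis wording, one more fixed effect and one more variance parameter. With 20 therapists and 4 patients each, a variance estimate will sometimes fall on zero, and the report should say so when it does. No change to recruitment, allocation or data collection is needed.

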### Power considerations

With respect to the differences between the two comparative conditions, based on prior studies with transdiagnostic disorders [94], social phobia [95], depression [96], and GAD [64], we planned to demonstrate a medium effect size of Cohen’s *d* = 0.40 between the implementation conditions on the outcome composite. Assuming an α error level of 0.05, a statistical power (1-Beta) of 0.80, and a correlation of 0.40 between the pre- and post-measurements, the proposed study of 40 participants in each condition treated by 20 therapists is able to detect such an effect size [97].

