### Assessments

For an overview of the assessments see Table 1. At intake, GAD-diagnosis and its core symptomatology is identified according to the structured interview section for GAD (DIPS; [72]). Furthermore, GAD-criteria are assessed using self-reports. The individual worries are identified using the Penn State Worry Questionnaire (PSWQ; [73]) and the Worry Domain Questionnaire (WDQ; [74, 75]). Mental disorders on Axis I are assessed using face-to-face diagnostic interviews (Strukturiertes Klinisches Interview für DSM, SKID-I; [76]).GAD-specific (primary) outcomes: The Penn State Worry Questionnaire (PSWQ; [73]) is a 16-item measure of the frequency and intensity of worry. It has considerable internal consistency (α = 0.86 in the prior trial). The Beck Anxiety Inventory (BAI; [77]) is a 21-item measure for anxiety symptoms (α = 0.92 in the prior trial).General (secondary) outcomes: The Beck Depression Inventory II (BDI-II; [78]) is a 21-item measure for depressive symptoms (α = 0.92 in the prior trial). The 9-item short version of the Symptom Check List (SCL-9; [79]) is an index for general severity (α = 0.86 in the prior trial). The short version of the Resource Self-Report Questionnaire (RES; [80]) measures various domains of individual and interpersonal strengths (α = 0.92 in the present sample).

**Table 1 Tab1:** Assessments

Measures	Assessment time					
	Recr.	Pre	S-by-S	Int.	Post	FU
Eligibility						
Structured Interview for DSM (SCID)	+					
GAD-diagnosis (DIPS)	+					
Worry Domains Questionnaire (WDQ)	+					
GAD-outcomes						
Beck Anxiety Inventory (BAI)		+		+	+	+
Penn State Worry Questionnaire (PSWQ)	+	+	1–16	+	+	+
General-outcomes						
Premature termination			1–16	+	+	+
Beck Depression Inventory (BDI)	+	+		+	+	+
Brief Symptom Inventory (BSI)		+		+	+	+
Resource potential questionnaire (RES)		+		+	+	+
Self-report process-measures						
Working Alliance Inventory - Patient (WAI-P)			1–16			
Working Alliance Inventory – Therapist (WAI-T)			1–16			
Bern Post-Session Report – Patient (BPSR-P)			1–16			
Bern Post-Session Report – Therapist (BPSR-T)			1–16			
Patients’ Therapy Expectation and Evaluation (PATHEV)		+		+		
Therapists’ preferences and outcome expectations	+ _1_					
Therapists’ self-reported focus on subtle changes			1–16			

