_1_At the beginning of the study, _2_ At the end of the study, *Recr*. Recruitment, *Pre* Intake assessment, *S-by-S* Session by session assessment, *Int.* Intermediate assessment (at session 5 and 10), *Post* Post assessment, *FU* Follow-up assessments (at 6- and 12-months after treatment termination)

In the prior trial, all GAD and general outcome self-report assessments were highly correlated (0.74 > *r* > 0.47) and a principal component factor analysis extracted one component that explained 67.5% of the total variance. For the purposes of the present trial, we therefore intend to include a standardized composite measure (“outcome composite”) that takes all the five GAD and general self-report measures into account (α = 0.73 in the prior trial; see also [81] for psychotherapy outcome definitions).(3)Post-session outcomes: The following process measures are examined: (a) Post-session outcomes (evaluated by therapists and patients): Working Alliance Inventory (WAI) [82, 83], Bern Post-Session Reports (BPSR) [84], and PSWQ patient self-report symptom status are conducted based on a session-by-session assessment from session 1 to 16. Furthermore, patient and therapist outcome expectations as well as therapist implementation preferences and in-session focus on subtle change will be assessed based on self-report items.(4)Safety outcomes: Suicidal ideation is assessed as safety outcome in the structured assessment at baseline, post, and follow-up measures and if indicated in every therapy session. As an outcome, suicidal ideation is assumed when the suicidal ideation item of the BDI is endorsed with a value > 1. In this case, individuals will be immediately contacted by telephone for further assessment and coordination as well as decisions for more appropriate treatments will be based on the general psychotherapeutic guidelines for suicidal ideation [85].

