### Statistical analysis

Along more traditional statistical approaches to handle the nested data structures, Longitudinal Multilevel Modeling (MLM) will be used to analyze the (intensive) longitudinal, nested data structures [86–89]. This data-analytical approach is specifically suitable to analyze the type of data that will be collected in the proposed implementation trial. For the primary research questions for post-session and treatment outcomes, MLM with time as a repeated within-group factor and implementation condition as a between-groups factor will be used [90]. A benefit of MLM, in comparison to traditional ANOVA with repeated measures lies in the individual parameterization of the process variables over various levels (repeated measures as random variables; [89]). The main analyses will be conducted on the intention-to-treat sample and the completer data. Between-group effect sizes will be based on pre-post within control Cohen’s *d*_ppwc_ suggested by Carlson and Schmidt [91] which is a mean difference estimate that takes into account both intake values at pretreatment and differences between each treatment condition.

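### The sample size rests on a five-scale composite that is never called primary, while PSWQ and BAI are called primary without a power statement; no single confirmatory outcome is fixed

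*Protocol article*

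**What the plan says.** All places are in the protocol article.

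- **Assessments, outcome list.** PSWQ and BAI stand under the primary label: "GAD-specific (primary) outcomes: The Penn State Worry Questionnaire" opens the entry and BAI follows under the same label. BDI-II, SCL-9 and RES are listed as general, secondary outcomes.
- **Assessments, composite.** A standardised composite is added that "takes all the five GAD and general self-report measures into account". It is labelled neither primary nor secondary.
- **Power considerations.** The only sample-size statement concerns a Cohen's d of 0.40 "between the implementation conditions on the outcome composite". Its other inputs are "Assuming an α error level of 0.05", "a statistical power (1-Beta) of 0.80", a pre-post correlation of 0.40 and 40 patients per condition.
- **Statistical exemplification.** The three-level model is for "repeated assessments of the primary outcome at level 1", in the singular. The equation is written for PSWQ and introduced as an example.
- **Aims.** The treatment-outcome question asks about primary and secondary self-reported outcomes. The composite is assigned to neither group.

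**The concern.** The outcome with a power statement is not declared primary, and the outcomes declared primary have no power statement. Three variables are therefore candidates for the confirmatory comparison of the two check-in strategies.

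What is at stake is how a positive result would be read. Without a fixed outcome, the trial could be reported as positive on whichever of PSWQ, BAI or the composite favours one condition. The Bias minimization section concedes a possible allegiance towards the prolonged-focus condition and says it may be hard to eliminate. A single outcome fixed in advance is a direct safeguard against that.

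An unseen analysis plan does not excuse this. Naming the primary outcome and tying the sample size to it belong in the protocol. The article does both, and the two do not agree.

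**Working it through.** **1. Statements side by side**

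| Variable | Label in Assessments | Power stated? | In the model section? |
|---|---|---|---|
| PSWQ | primary | no | yes, as the example |
| BAI | primary | no | not named |
| Composite of five | none | yes | not named |

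No row is both labelled primary and powered.

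**2. The plan's own figure**

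Inputs from Power considerations: d = 0.40, alpha 0.05, correlation 0.40, 40 per arm. Two-sided power is Φ(d / (s·√(2/40)) − 1.96), with √(2/40) = 0.2236.

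- Post score only, s = 1: 0.40/0.2236 = 1.789, power 0.43.
- Baseline-adjusted, s = √(1 − 0.40²) = 0.917: 1.952, power 0.50.
- Change score, s = √(2(1 − 0.40)) = 1.095: 1.633, power 0.37.

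The noncentral t gives 0.42, 0.49 and 0.36. Two-sided 80% power needs 99, 83 or 118 per arm respectively. A repeated-measures interaction with f = 0.20 and two measurements gives 0.90 at N = 80 and needs N = 62, so it does not reproduce the stated pair either. On that reading λ = 0.20²·80·2/(1 − 0.40) = 10.67 and √10.67 = 3.27. That equals a difference in change of 3.27·1.095·0.2236 = 0.80 SD, not 0.40. All figures assume no dropout and no therapist clustering. The stated power was therefore not reproduced from its inputs. That is a separate matter, but it means the power statement is no reason by itself to prefer the composite.

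**3. Does the power statement carry over to PSWQ or BAI?**

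Assume that all five scales share one standardised effect δ and one correlation r. Then the composite has d = δ·5/√(5 + 20r), so δ = 0.40·√((1 + 4r)/5).

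- r = 0.47: δ = 0.40·√0.576 = 0.30.
- r = 0.74: δ = 0.40·√0.792 = 0.36.

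Baseline-adjusted power at 40 per arm is then about 32% to 41%, against 50% for the composite by the same formula. Which outcome is chosen matters.

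**4. False-positive chance under an any-one-suffices rule**

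Assumptions: each test is two-sided at 0.05, any one suffices, and the prior-trial scale correlations (0.47 to 0.74, Assessments) are taken as the correlations between tests. The composite is equally weighted, so a single scale correlates √((1 + 4r)/5) with it. The chance is 1 − P(all |Z| ≤ 1.96) under a multivariate normal, by simulation with 1.5 million draws.

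| r | Scale with composite | PSWQ or BAI | PSWQ, BAI or composite |
|---|---|---|---|
| 0.47 | 0.76 | 0.092 | 0.110 |
| 0.60 | 0.82 | 0.088 | 0.101 |
| 0.74 | 0.89 | 0.081 | 0.091 |

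Under independence the figures would be 1 − 0.95² = 0.0975 and 1 − 0.95³ = 0.143. These overstate the case, because the outcomes overlap and correlate.

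**The case against.** Four points can be made for the plan.

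- **Alpha.** A reader might infer that each outcome is to be tested at an unadjusted 0.05. The article does not say so. Alpha appears once, as an input to the composite's power statement, and a multiplicity rule may sit in an analysis plan that is not shown. This stands: the error rates are conditional illustrations, not properties of the trial.
- **The PSWQ equation.** A reader might take it as the primary analysis, to the exclusion of the others. It is expressly an example, and PSWQ is one of the labelled primaries, so it excludes neither BAI nor the composite. This also stands. What remains from that section is the singular reference to a primary outcome where Assessments lists two. That could be loose wording, but it leaves the question open.
- **Post-session outcomes and completers.** The Statistical analysis section begins a sentence "For the primary research questions for post-session and treatment outcomes", and a reader might infer that post-session measures are further primary outcomes. The phrase concerns research questions, and Assessments lists those measures separately as process measures. The same section plans main analyses in intention-to-treat and completer data. Counting the completer results as extra chances of success would need an assumed overlap and a success rule that the article does not contain, so no figure is given.
- **Correlations.** The range 0.47 to 0.74 describes scale scores in the prior trial. The planned tests concern change over time, and the article gives no correlations between changes. This stands as a limit on the error rates.

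None of this reconciles the primary labels in Assessments with the outcome used in Power considerations.

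**Conclusion.** The concern holds as a conflict between stated designations. The composite is powered but not primary, PSWQ and BAI are primary but not powered, and one section assumes a single primary outcome that no section identifies. This rests on the text alone and needs no assumption.

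The size is conditional. With three tests at 0.05, an any-one-suffices rule and correlations of 0.47 to 0.74, the chance of at least one false positive would be about 0.09 to 0.11; for PSWQ or BAI alone, about 0.08 to 0.09. The documents do not support saying that the trial will be tested in this way. They do support saying that nothing in the article rules it out. The confirmatory outcome should be settled before outcome data are seen, because the meaning of a positive result depends on it.

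**What to change.** 1. Declare one confirmatory outcome, tested at alpha 0.05, and use the same designation in Assessments, Statistical analysis and Power considerations. Either candidate is defensible:
   - **The composite**, after settling its general-severity scale, which is SCL-9 in the text but BSI in Table 1.
   - **PSWQ**, with an effect size justified for PSWQ itself rather than carried over from the composite.
2. Restate the power for the chosen outcome, with the test and its sidedness given. This is needed for the composite too, since its present figure could not be reproduced.
3. Make the remaining outcomes secondary. Apply a multiplicity adjustment, such as Holm, to any on which a claim is to be made.

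The designation costs only wording. The downside is small: BAI and either PSWQ or the composite cannot then serve as the confirmatory outcome. Restating the power may show that 80 patients give less than 80%, but the choice of outcome does not create that problem. Keeping three co-equal outcomes would cost more. With a Bonferroni split (0.05/3 = 0.0167) and d = 0.40, 80% power needs 110 per arm baseline-adjusted, 131 on the post score or 158 on the change score, against 83, 99 and 118 at 0.05.

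### The stated 80% power for d = 0.40 with 40 patients per condition does not follow from the protocol's own inputs, which give about 36% to 49% two-sided

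*Protocol article*

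**What the plan says.** The section Power considerations of the protocol article sets the target effect at a Cohen's d of "0.40 between the implementation conditions on the outcome composite". The other inputs are given as "Assuming an α error level of 0.05", then "a statistical power (1-Beta) of 0.80, and a correlation of 0.40 between the pre- and post-measurements". The conclusion is that "the proposed study of 40 participants in each condition treated by 20 therapists is able to detect such an effect size". Sidedness, the test and the number of measurement occasions are not stated; a reference is cited for the method.

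Three other places bear on which test is meant:

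- Design: "Eighty patients will be allocated within a traditional 2 × 4 randomized controlled design", with assessment time as the within-subject factor.
- Statistical analysis: the between-group effect size is "a mean difference estimate that takes into account both intake values at pretreatment and differences between each treatment condition".
- Statistical exemplification: a three-level growth model in which implementation condition acts on the time slope, not on the level of the scores.

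**The concern.** An effect size, an α level, a pre-post correlation and a group size are enough to compute power for any standard two-occasion comparison. The stated 0.80 can therefore be checked by arithmetic and does not depend on detail that an article leaves to a fuller document. For two independent groups, 40 per arm is well short of what d = 0.40 usually needs, and a correlation of only 0.40 removes little variance by baseline adjustment and increases it for a change score.

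The paragraph is the article's only justification of the sample size. If the figure is wrong, the trial has an even chance or less of detecting the effect it was planned for. Both arms deliver the same treatment package, so a small or non-significant difference is a realistic outcome, and its interpretation depends on what the trial could have detected.

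**Working it through.** **Inputs (Power considerations):** d = 0.40 on a scale with SD 1; α = 0.05; pre-post correlation r = 0.40; n = 40 per condition; claimed power 0.80. **Assumed:** a two-sided test (one-sided also shown), no dropout and no therapist variance.

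**1. Two-occasion analyses.** Power comes from the noncentral t distribution with noncentrality ncp = (d / k) × √(n/2) = (0.40 / k) × √20, where k is the SD of the analysed quantity:

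- Post score: k = 1.
- Change score: k = √(2(1 − r)) = √1.2 = 1.095.
- Baseline-adjusted (ANCOVA): k = √(1 − r²) = √0.84 = 0.917.

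| Analysis | ncp | df | Two-sided power | One-sided power | d detectable at 80% (two-sided) | n per arm for d = 0.40 at 80% |
|---|---|---|---|---|---|---|
| Change score | 1.633 | 78 | 36.4% | 49.0% | 0.69 | 119 |
| Post score | 1.789 | 78 | 42.4% | 55.1% | 0.63 | 100 |
| Baseline-adjusted | 1.952 | 77 | 48.7% | 61.4% | 0.58 | 84 |

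The stated 0.80 is not reproduced by any row. To reach it with 40 per arm, the pre-post correlation would have to be about 0.78 (baseline-adjusted) or 0.80 (change score), about twice the stated value.

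**2. The same contrast as a 2 × 2 group-by-time interaction.** A difference of 0.40 in change corresponds to f = d/4 = 0.10. Then λ = N f² m / (1 − r) = 80 × 0.01 × 2 / 0.6 = 2.67, and power is 36.4%, as for the change score. Entering f = d/2 = 0.20 gives λ = 80 × 0.04 × 2 / 0.6 = 10.67 and power 89.7%, with 80% already reached at a total of 62. That matches neither 0.80 nor 80 patients, and it implies a 0.80 SD difference in change, twice the planned effect.

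**3. A slope test, closer to the growth model.** Table 1 and its footnote place the outcome scales at pre, sessions 5 and 10, and post. Take times 0, 5, 10 and 16, every correlation at 0.40 (compound symmetry) and a difference that grows linearly to 0.40 at the end.

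- Mean time = 7.75. Sum of squares about the mean = 60.0625 + 7.5625 + 5.0625 + 68.0625 = 140.75.
- Slope difference = 0.40 / 16 = 0.025.
- SD of a patient's slope = √(0.6 / 140.75) = 0.0653.
- ncp = (0.025 / 0.0653) × √20 = 1.71, so power = 39.4%.

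With equally spaced occasions the result is 39.8%.

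**4. A route that does reach about 0.80.** Take a baseline-adjusted comparison of the mean of four post-baseline scores, with a constant effect of 0.40 at each and every correlation at 0.40. The variance is (1 + 3 × 0.40)/4 − 0.16 = 0.39, ncp = 0.40 / √0.39 × √20 = 2.86, and power is 80.7%. With three or five post-baseline scores it is 75.9% or 83.7%.

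**The case against.** The strongest defence is step 4. The article describes a repeated-measures design, the composite's scales are scheduled at several occasions after baseline, and averaging four of them gives almost exactly the stated power. The cited method reference is not available here and might contain such a calculation. What stands is that 36% to 49% is conditional on a two-sided, two-occasion analysis, and the point has to be worded that way. The route does not rescue the claim as written. The power paragraph mentions only pre- and post-measurements, and a constant full effect from the first averaged assessment is nowhere stated. The exemplified growth model tests a difference in slope, for which power is about 39% to 40%.

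A second defence is that each therapist treats patients in both conditions, so therapist variance drops out of the comparison. Under assumed intraclass correlations of 0.05 to 0.20 this lifts power to at most 57%. The growth model also lets the condition effect vary between therapists, which works the other way. The article gives no therapist variance and no dropout rate. Such detail may sit in a fuller document, and the error does not depend on it.

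A reader might infer that the protocol would present a null result as evidence that the two conditions do not differ. The article does not support that: it claims no equivalence and does not say how a null result would be read. Nor does the arithmetic show that the planned multilevel analysis should be replaced by a baseline-adjusted one. The error lies in the power statement, not in the choice of model. Finally, the first listed research question, practicability of the design, does not rest on this figure.

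**Conclusion.** The stated power of 0.80 for d = 0.40 with 40 per condition is not reproduced from the inputs beside it. Two-sided power is about 36% (change score or group-by-time), 42% (post score) or 49% (baseline-adjusted). It is at most 61% one-sided, and about 39% to 40% for a linear slope test over the four composite assessments from pre to post under compound symmetry. At 80% power the detectable d is about 0.69, 0.63 or 0.58 for the change, post and baseline-adjusted analyses. A non-significant result would therefore be uninformative about d = 0.40; whether anyone would misread it is a separate question on which the article is silent.

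The figures take the article's d, α, correlation and group size as given, with no dropout and no therapist variance. Sidedness is an assumption, but a one-sided test does not change the conclusion. The one variant found near 0.80 needs assumptions that the article does not state and that do not fit its slope model.

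**What to change.** Keep 80 patients and correct the power paragraph. State power and detectable effect for the analysis actually planned, and name the test, its sidedness and the measurement occasions. On the present inputs that is about 36% to 40% for a change or slope contrast, or about 49% if a baseline-adjusted post comparison is the one to be used.

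If the sponsor did rely on more than two occasions, the alternative is to write out and justify the assumptions that produce 0.80: for example, the mean of four post-baseline assessments, a constant 0.40 effect at each, and every correlation at 0.40. That analysis would then have to be reconciled with the slope model in Statistical exemplification.

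The cost is that the stated power becomes less favourable. Restating it for the planned analysis is a change of wording and needs no change to the sample size, allocation or analysis model.
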